## Abstract

**Background:**

The incidence and prevalence of chronic diseases have reached epidemic proportions during the last decades and are not expected to diminish. Chronic diseases increasingly affect younger individuals too, with over 40% of all deaths due to non-communicable diseases occurring before the age of 70. This has led to the development of information services aimed at preventive health care, such as *Health Potential®*. This counselling service estimates a personal disease risk of a carefully selected list of preventable common chronic diseases that have both a genetic and a lifestyle component of development. The results are delivered face-to-face by a lifestyle counsellor, simultaneously stimulating initial steps towards behaviour change. This information can assist in lifestyle decision-making.

**Methods/design:**

The primary aim is to study the effect of the Health Potential® service on change in lifestyle behaviour in distinguishable customer populations. The secondary aims are (1) to study the effect of the Health Potential® service on determinants of behaviour change, (2) to study the effect of additional lifestyle counselling on behaviour change and determinants thereof, and (3) to describe the characteristics of the Health Potential® customer. The study consists of two integrated designs: (A) a two-armed non-randomised controlled pre-test/post-test trial (1.5:1 ratio), followed by (B) a two-armed randomised controlled pre-test/post-test trial (1:1 ratio), resulting in three study arms. Participants are clients of local prevention clinics, purchasing a personalised health check (PHC; intervention condition), consisting of Health Potential® and a general health check, or the general health check alone (GHC; control condition) (part A). PHC participants will be randomised to receive four additional lifestyle counselling sessions over a period of 3 months (part B).

**Discussion:**

This research can provide valuable insights into the effectiveness of and possible ways forward in the field of personalised prevention making use of lifestyle interventions enriched with modern genetic advancements.

**Trial registration:**

Nederlands Trial Register, NTR6289 and NTR6288. Registered on 24 February 2017.

**Electronic supplementary material:**

The online version of this article (10.1186/s13063-018-2630-7) contains supplementary material, which is available to authorized users.

## Background

The incidence and prevalence of chronic diseases have reached epidemic proportions during the last decades and are not expected to decrease or diminish. In 2012, 38 million people died as a result of a non-communicable disease, of which 82% were due to cardiovascular diseases, diabetes, cancer and chronic respiratory diseases [1]. This number is projected to increase to 52 million deaths by 2030 [2]. Of particular concern is the fact that over 40% of all NCD deaths occurred before the age of 70 in 2012 [1]. As a result of these developments, we must expect an increasing economic burden and reduction of quality of life in many societies, among both affected people and their social environment.

Most, if not all, common chronic diseases develop over a lifetime as a result of interplay between genetic predisposition and the accumulation of lifetime exposures to environmental and behavioural factors. According to the World Health Organization (WHO), unhealthy diet, physical inactivity, tobacco use and harmful alcohol consumption are among the most important modifiable causes of chronic disease worldwide [3]. For example, harmful alcohol use and tobacco use account for 12% of all deaths worldwide, and an additional 19% is accounted for by unhealthy diet and physical inactivity [3]. As these are all modifiable, great potential exists for prevention or delay of chronic diseases, resulting in a renewed necessity for and interest in disease prediction and prevention [4].

The fact that most chronic diseases seem to be preventable and the neoliberal political climate in many countries have contributed to the rise of personal responsibility for health [5]. Individuals are more and more expected to strive to obtain and maintain their best possible health. In order to do so, they need to be optimally informed and make their own risk-benefit analyses. This has led to an exponential growth in services aiming at assisting in informing and assisting individuals to make informed decisions. Another such approach is through genetic testing [6]. Although one has no control over their genetic make-up, knowledge of genetic predispositions could provide the opportunity for personalised prevention strategies and may serve in health-related decision-making [7, 8].

Personal genomic testing (PGT) uses genetic variations in individuals to estimate personal disease risks and sometimes several other genetically determined phenotypes such as food intolerances or drug metabolism [9]. PGT has become popular and accessible as a result of rapid advances in the field of DNA analysis techniques. This has made genome analysis possible at relatively low costs, with PGT companies like 23andMe dropping their price from US$999 in 2007 to US$199 in 2017 ([10], https://www.23andme.com/). These services are mostly offered to the general population direct-to-consumer (DTC), meaning without interference of a physician. PGT may help individuals change their behaviour towards more health-promoting lifestyle through identification of an increased disease risk [11]. An important assumption of the success of this strategy is that the identification of increased disease risk could directly influence risk reduction behaviours [8, 12, 13]. However, research has shown that this assumption mostly does not apply in all populations or that the effects are minor in general populations [13, 14].

Limitations of this idea that PGT may facilitate behaviour change are that, firstly, probability and genetic data are difficult to comprehend without counselling [15, 16] and understanding is strongly influenced by several factors such as the format of delivery [17]. Secondly, disease risks are not solely determined by either lifestyle or genetic factors, but both [18]. Thirdly, disease risk information alone may not be motivating enough for individuals to change behaviour and therefore additional lifestyle intervention and motivational counselling may be necessary to help individuals change and maintain behaviour [7].

To address these shortcomings, a new disease risk information service has been developed: *Health Potential®*. This service estimates a personal disease risk of a carefully selected list of preventable common chronic diseases that have both a genetic and a lifestyle component of development. The results are delivered face-to-face by a certified lifestyle counsellor, simultaneously stimulating initial steps towards behaviour change. Because previous research has shown that not all health care professionals feel confident in interpreting and communicating DTC-GT results to their patients or clients [19, 20], all Health Potential® counsellors are trained to ensure confidence and skill.

The effect of this new personalised service will be researched in two integrated studies, one observational study and one intervention trial, comparing the service to a general health check only. The primary aim of the study is to study the effect of the Health Potential® advice on change in lifestyle behaviour in distinguishable customer populations. The secondary aims are (1) to study the effect of the Health Potential® service on determinants of behaviour change, (2) to study the effect of additional lifestyle counselling on behaviour change and determinants thereof, and (3) to study the characteristics of the Health Potential® customer.

## Methods/design

### Study design

This study consists of two integrated trials. The first trial is a non-randomised two-armed controlled pre-test/post-test superiority trial (part A). Of one of those arms, participants can enter the second trial, which is a randomised controlled pre-test/post-test superiority trial (part B), on the condition that they consent to participate. In order to obtain sufficient participants for part B, participants in part A will be distributed in a 1.5:1 ratio. Participants will be randomised at a 1:1 ratio in part B. This results in three study arms (Fig. 1). However, due to eligible participants of part A potentially not consenting to participation in part B, study arm 2 can again be considered as two study arms: participants in arm 2a have consented to participate in part B whereas participants in 2b have not (see Fig. 1 for a visualisation).

**Fig. 1 Fig1:**
[figure not shown]
Conceptual framework

#### Rationale for the study design

The study is designed in a way to reflect the ‘real world’ situation in which the participants are not randomised for part A and all participants pay a (reduced) fee for the services. The reason behind this approach is that we expect a certain level of ‘pre-motivation’ and possibly other different personal characteristics (e.g. personality, socio-economic status, income, level of education, gender, age) among clients of the Health Potential® service, particularly when an additional ‘barrier’ exists of a fee that has to be paid for the service.

Due to the nature and cost of the products, and consistent with Rogers’ theory of early adopters [21], the study population is likely to consist of (apparently) healthy individuals aged 18 and over, expected to have higher social status, higher financial resources, and higher education, and who are relatively health conscious.

### Study setting

Part A of the study takes place through online questionnaires, which participants can fill out at home. The additional lifestyle counselling will be offered through certified counsellors located in South-Limburg, The Netherlands.

### Participants and recruitment

Participants for part A of the study will be recruited from the regular customers at local prevention clinics who have purchased one of the following products:Product 1: *personalised health check* (PHC). The PHC consists of the Health Potential® service (future health) and a general health check of the customer’s current health.Product 2: a general health check of current health only (GHC).

Potential participants will be informed of the study by the local responsible investigator of each clinic. Eligible participants for part A are apparently healthy individuals aged 18 and over, with a Dutch language level similar to language proficiency level B2, not currently following any prescribed dietary or other guidelines, not pregnant or trying to become pregnant, authorised to make autonomous decisions, able to independently visit the counselling clinic, and have Internet access and an email address. Participants who purchased product 1 are eligible to take part in part B of the study. Enrolment will be open for 1 year.

### Sample size and power calculation

The sample size calculation is based on the proportion of participants who have changed their behaviour (being in the action/maintenance stage of behaviour change; see ‘Study parameters’) for at least three of the received advices at follow-up in the overall analysis. The type I error rate was set at 0.05 and an additional 20% was added to compensate for loss to follow-up in part A.

*Part A*: The smallest difference is expected between arms 2 and 3. It is estimated that with (291 + 20%=) 350 participants in each arm, part A has a power of 80% to detect a proportion of 0.3 in arm 2 versus a proportion of 0.2 in arm 3.

*Part B*: Study arm 1 will be compared to arm 2a. It is then estimated that with (160 + 20%=) 192 participants in each arm, part B has a power of 80% to detect a proportion of 0.45 in arm 1 versus a proportion of 0.3 in arm 2a. As in part A 548 participants will be included in the PHC condition, this will give a margin of (548 − 384=) 164 for participants not consenting to participate in part B. Together this results in a total number of participants of (192 + 350 + 350=) 892.

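### Loss to follow-up is covered by multiplying by 1.2, which protects 80% power only up to about 17% loss; if the 20% is the loss allowed for, power is about 78.5% in both parts (minor)

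*Protocol article*

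**What the plan says.** Everything is in the protocol article, section Sample size and power calculation, with the allocation ratios under Study design.

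- Error rate: "The type I error rate was set at 0.05". The section does not say whether the test is one- or two-sided.
- Loss: "an additional 20% was added to compensate for loss to follow-up in part A". This sentence names Part A only, but the same 20% is then added in Part B.
- Part A: "It is estimated that with (291 + 20%=) 350 participants in each arm, part A has a power of 80" per cent, "to detect a proportion of 0.3 in arm 2 versus a proportion of 0.2 in arm 3".
- Part B: "It is then estimated that with (160 + 20%=) 192 participants in each arm, part B has a power of 80" per cent, "to detect a proportion of 0.45 in arm 1 versus a proportion of 0.3 in arm 2a".

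Both power statements are for equal arms. The 1.5:1 ratio in Study design describes all clients with the personalised health check (PHC) against those with the general check, not arm 2 against arm 3. No expected loss rate is given anywhere in the article.

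**The concern.** Adding 20% to a required number does not protect it against a 20% loss, because the loss is taken from the larger, inflated number. A reader who sees a 20% allowance for loss will assume that the trial keeps 80% power if one participant in five drops out. With the printed targets it does not: the allowance runs out at about 17%.

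The 80% statement also depends on a loss condition that the section never states. With no loss, 350 and 192 per arm give about 87% power by the plan's own formula. So 80% at those sizes can only refer to what is left after loss, and the amount of loss matters. Outcomes are collected by online questionnaire up to 1 year, so the loss that can be tolerated should be stated correctly.

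**Working it through.** **Inputs** (Sample size and power calculation): alpha 0.05; power 80%; 0.30 v 0.20 in Part A; 0.45 v 0.30 in Part B; equal arms. A two-sided test is an assumption. It is supported by the match in step 1; the one-sided versions give about 229 to 251 (Part A) and 126 to 141 (Part B), which do not match.

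**1. Reproduce the plan's base numbers.** Unpooled variance, no continuity correction:

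n = (z₀.₉₇₅ + z₀.₈₀)² × [p₁(1 − p₁) + p₂(1 − p₂)] / (p₁ − p₂)², with (1.960 + 0.842)² = 7.849.

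- Part A: 7.849 × (0.21 + 0.16) / 0.01 = 290.4, rounded up to 291. Matches.
- Part B: 7.849 × (0.2475 + 0.21) / 0.0225 = 159.6, rounded up to 160. Matches.

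So 291 and 160 are analysable numbers with no hidden reserve.

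**2. Reproduce the inflation.**

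- Part A: 291 × 1.2 = 349.2, given as 350.
- Part B: 160 × 1.2 = 192.

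**3. Inflation that would cover a 20% loss,** n / (1 − 0.20):

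- Part A: 291 / 0.8 = 363.75, so 364, which is 14 per arm more than 350.
- Part B: 160 / 0.8 = 200, which is 8 per arm more than 192.

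**4. Power at the printed sizes,** from Φ(|p₁ − p₂| / √{[p₁(1 − p₁) + p₂(1 − p₂)] / n} − 1.960):

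| | Part A | Part B |
|---|---|---|
| No loss | n = 350: 86.8% | n = 192: 86.7% |
| 20% loss | n = 280: 78.6% | n = 153.6: 78.5% |

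For Part A at 280: √(0.37 / 280) = 0.03635; 0.10 / 0.03635 = 2.751; Φ(0.791) = 0.786. For Part B at 153.6: √(0.4575 / 153.6) = 0.05458; 0.15 / 0.05458 = 2.748; Φ(0.789) = 0.785. Rounding Part B down to 153 completers gives 78.3%.

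**5. Largest loss that still leaves the required number.**

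- Part A: 1 − 291/350 = 16.9%.
- Part B: 1 − 160/192 = 16.7%.

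**6. Sensitivity to the variance formula.** With the pooled formula the required numbers are 294 and 163, power at 20% loss is 78.2% and 77.8%, and the loss limits are 16.0% and 15.1%. The largest shortfall found is 2.4 points (Part B, pooled, 153 completers: 77.6%). Pooled and unpooled figures should not be mixed in one statement.

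**7. The totals in the same section.** The three arms are summed as 192 + 350 + 350 = 892. The section also plans 548 PHC participants, and with 350 in arm 3 that makes 898. On the second count arm 2 has 548 − 192 = 356. With 20% loss that leaves 284.8 v 280: √(0.21/284.8 + 0.16/280) = 0.03618, and Φ(0.10/0.03618 − 1.960) = Φ(0.804) = 78.9%. This is still below 80%.

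**The case against.** The strongest reply is that the article never says 20% of participants are expected to be lost. It says that 20% was added, and the arithmetic does what the words say. A 20% addition fully covers a loss of about 16.7%, so on a literal reading the section does not contradict itself, and the full protocols it points to may give a loss rate. This stands in part. A reader might infer that the plan states a 20% loss and that both parts therefore miss their stated power. The article does not support that: the shortfall depends on taking the 20% as the loss rate. What remains is that 20% is the only loss figure given, that its purpose is to offset loss, and that the 80% statement needs a loss condition which the inflation meets only to about 17%.

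The second reply is that the effect is small, and that stands in full. The assumed proportions matter far more. With 291 per arm, 0.29 instead of 0.30 in arm 2 gives about 72% power, and 0.31 gives about 87%. A reader might conclude from the present point that the trial is materially underpowered; a loss of about 1.5 points does not support that.

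The choice of the unpooled formula is not itself an error. It is standard, it differs from the pooled one by 3 per arm, and the article names no test that would require the other.

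**Conclusion.** The point holds as a minor, conditional one. If the 20% is the loss allowed for, the inflation is done wrongly: the targets should be 364 and 200 per arm rather than 350 and 192, about 4% more. At the printed targets, power at 20% loss is about 78.6% in Part A (arms of 350) and 78.5% in Part B, against a stated 80%. If the intended loss is about 17% or less, the sizes are adequate and only the loss rate needs stating.

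The conclusion rests on a two-sided test and the unpooled formula, both inferred from the exact match to 291 and 160, and on equal loss in the two arms of each comparison.

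**What to change.** State the assumed loss rate, and replace the unconditional power statements with something like: at 350 and 192 per arm, 80% power (two-sided, unpooled variance) is kept for loss up to 16.9% in Part A and 16.7% in Part B, and is about 78.5% in both parts at 20% loss. This costs a sentence and a slightly less favourable figure, and needs no extra participants.

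If the targets are reset for any reason, use n / (1 − loss). At 20% loss that means 364 and 200 per arm, which adds 8 + 14 + 14 = 36 to the plan's three-arm sum.

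When the paragraph is revised, do not carry 892 forward as the confirmed total. Reconcile it with the 548 PHC participants plus 350 in arm 3 (898) in the same section, and give one set of arm sizes.

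### The part B non-consent margin of 164 rests on 548 PHC participants, but the stated total of 892 contains only 542, which gives a margin of 158

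*Protocol article*

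**What the plan says.** All the counts are in the protocol article, section 'Sample size and power calculation'.

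- Part A compares arm 2 with arm 3: "It is estimated that with (291 + 20%=) 350 participants in each arm".
- Part B compares arm 1 with arm 2a: "It is then estimated that with (160 + 20%=) 192 participants in each arm".
- The PHC count, used to work out how many may decline part B, is: "As in part A 548 participants will be included in the PHC condition". Subtracting 384 (two arms of 192) gives the stated margin of 164.
- The overall size follows: "Together this results in a total number of participants of (192 + 350 + 350=) 892".

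The section 'Study design' adds that "participants in part A will be distributed in a 1.5:1 ratio", so that part B has enough participants. The abstract repeats this ratio without counts. 'Study design' also divides arm 2 into those who consented to part B (2a) and those who did not (2b). 'Participants and recruitment' makes purchasers of the PHC the people eligible for part B. The PHC condition is therefore arm 1 plus arm 2, and the GHC condition is arm 3.

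**The concern.** The margin and the total sit in adjoining sentences and depend on the same quantity, the number of PHC participants, yet they imply different values for it.

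This matters for two reasons. First, part A is not randomised: people enter by the product they bought, so no allocation list fixes the arm sizes and the stated counts are what recruitment works to. Second, the article gives the supply of part B participants as the reason for the unequal split. The allowance for non-consent is what that split is meant to secure, and it is derived from the count that does not agree with the total.

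**Working it through.** **Inputs** (all from 'Sample size and power calculation' unless noted): 291 and 160 per arm before inflation; 350 and 192 after it; PHC 548; margin 164; total 892; proportions 0.3 v 0.2 (part A) and 0.45 v 0.3 (part B); 80% power; type I error 0.05. Sidedness is not stated; I assume two-sided because it reproduces the stated sizes. The ratio of 1.5:1 is from 'Study design'.

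**Step 1. Reproduce the per-arm sizes.** Two proportions, unpooled variance:

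n = (1.96 + 0.8416)² × [p1(1 − p1) + p2(1 − p2)] / (p1 − p2)²

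- Part A: 7.849 × (0.21 + 0.16) / 0.01 = 290.4, rounded up to 291. Stated: 291.
- Part B: 7.849 × (0.2475 + 0.21) / 0.0225 = 159.6, rounded up to 160. Stated: 160.
- Inflation as n × 1.2: 291 × 1.2 = 349.2, rounded up to 350; 160 × 1.2 = 192. Both match.

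**Step 2. Reproduce the total.** 192 + 350 + 350 = 892. Matches.

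**Step 3. Try to reproduce the PHC count.**

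- Sum of the PHC arms: 192 + 350 = 542. Stated: 548.
- Total less GHC: 892 − 350 = 542. Again not 548.

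The subtraction 548 − 384 = 164 is itself correct, and 548 appears twice. The discrepancy is in the count that goes in, not in the subtraction.

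**Step 4. What each choice implies.**

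| What is held fixed | PHC | GHC | Total | Margin over 384 | Part B consent required |
|---|---|---|---|---|---|
| Arm sizes and total | 542 | 350 | 892 | 542 − 384 = 158 | 384/542 = 70.8% |
| PHC 548 and GHC 350 | 548 | 350 | 898 | 548 − 384 = 164 | 384/548 = 70.1% |
| PHC 548 and total 892 | 548 | 344 | 892 | 164 | 70.1% |

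The third row leaves GHC six short of the 350 per arm in the part A power statement. No row holds 548, 350 and 892 together.

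**Step 5. Ratio.** 542/350 = 1.549 and 548/350 = 1.566. To one decimal place the first gives 1.5 and the second 1.6.

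**Step 6. Effect on power.** With PHC at 542, arm 1 has 192 and arm 2 has 350. With PHC at 548, arm 1 has 192 and arm 2 has 356. With GHC at 350, both meet the planned arm sizes in parts A and B, so neither power statement changes.

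**The case against.** The best case for leaving this alone is its size. The difference is six people in 892 (0.7%), and the required part B consent moves by less than one percentage point. Every other figure in the section reproduces. All of that stands and sets the severity. It does not remove the error: these are stated whole numbers being added, so no rounding or choice of formula reconciles them. Nor is this detail that an article leaves to the full protocol, because the article prints both figures.

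A reader might go further and infer that the 1.5:1 ratio sets a third PHC target, 1.5 × 350 = 525, which would leave 525 − 192 = 333 in arm 2 and a margin of 525 − 384 = 141. The document does not support this. It never applies the ratio to 350. In a non-randomised part, where people choose which product to buy, 1.5:1 reads naturally as an approximate split, and 542/350 rounds to it.

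A reader might also infer that part A power falls to about 77%. That figure needs the exact-ratio reading and also takes 20% loss as n × 0.8 (266 v 280 analysed, 77.4%). Most of the shortfall from 80% has nothing to do with the PHC count: 350 per arm with n × 0.8 leaves 280 per arm and 78.6% power, with no ratio question at all. That comes from the inflation convention and should not be charged to this discrepancy.

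**Conclusion.** The point holds as a minor figure that is wrong as written. The margin is computed from 548 PHC participants, while the total contains 542. If the total of 892 is right, the margin is 158 rather than 164 and the required consent is 70.8% rather than 70.1%. If 548 is right, the total is 898.

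This rests only on the PHC condition being arms 1 and 2, which the article's arm structure and part B eligibility establish, and on addition of its own numbers. The document does not show where 548 comes from, so it cannot be said which figure was intended. Planned arm sizes, stated power and the comparisons are unaffected.

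**What to change.** Use one PHC figure throughout 'Sample size and power calculation'. Either of two sets is consistent:

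- PHC 542, margin 158, total 892, which follows from the stated arm sizes; or
- PHC 548, margin 164, total 898, with arm 2 then at 356.

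In 'Study design' and the abstract, describe the part A ratio as approximately 1.5:1 (542/350 is about 1.55); a more precise ratio is not needed for a non-randomised split. Check the full protocols for parts A and B for the same figures.

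The cost is a correction of stated numbers. The article gives the trial status as in preparation, so the agreed target can be set before recruitment starts. The first option changes no recruitment total; the second adds six participants to it.

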### Blinding, randomisation and treatment allocation

Participants who purchased the PHC and who consented to participate in part B will be electronically randomised to receive the additional lifestyle counselling. Randomisation will be stratified by local clinic, and block randomisation will be used with block sizes of 4 within each stratum. The health coach will subsequently implement the appropriate intervention.

Although blinding is not possible for the participants and the health counsellors delivering the intervention, the data analyses will be performed in a blinded format through preparation of the dataset by an independent researcher.

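### The 164 PHC non-consenters are not pure slack: with no stated cap on Part B, arm 2 drops below its planned 350 once consent exceeds about 72%

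*Protocol article*

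**What the plan says.** All of the figures are in the Protocol article, Sample size and power calculation.

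- **Part A** compares arm 2 with arm 3: "The smallest difference is expected between arms 2 and 3". The size is "291 + 20%=) 350 participants in each arm", chosen for 80% power when the true rates are 0.3 (arm 2) and 0.2 (arm 3).
- **Part B** compares arm 1 with arm 2a, with "160 + 20%=) 192 participants in each arm", for 80% power to detect 0.45 against 0.3.
- **PHC intake:** "As in part A 548 participants will be included in the PHC condition". From this the article takes 548 − 384 = 164 as its margin for non-consent.
- **Total:** 192 + 350 + 350 = 892.

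The Study design section splits arm 2 into 2a (consented to Part B) and 2b (did not consent) and sets 1:1 allocation in Part B. The Blinding, randomisation and treatment allocation section says: "Participants who purchased the PHC and who consented to participate in part B will be electronically randomised". Neither section states a maximum number to be randomised.

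**The concern.** Calling 164 a margin suggests that the plan is safe if few clients decline. That is true for Part B but not for Part A. Each pair of extra consenters sends one more person to arm 1 and takes one from arm 2, so arm 2 depends on a minimum number of decliners to reach 350. Part A addresses the primary aim, and its stated size and power then rest on an upper consent limit that the article does not give. High consent is conceivable, because the rationale for the design expects motivated, health-conscious clients.

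**Working it through.** **Inputs** (all from the article): alpha 0.05; Part A rates 0.3 and 0.2; Part B rates 0.45 and 0.3; power 80%; enrolment = evaluable × 1.2; arm 3 = 350; PHC clients N = 548. Sidedness is not stated; two-sided reproduces the figures.

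**Reproducing the stated sizes.** The unpooled two-proportion formula is n = (1.960 + 0.842)² × [p₁(1 − p₁) + p₂(1 − p₂)] / (p₁ − p₂)².

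- Part A: 7.849 × (0.21 + 0.16) / 0.01 gives 291 after rounding up; 291 × 1.2 = 349.2, so 350.
- Part B: 7.849 × (0.2475 + 0.21) / 0.0225 gives 160; 160 × 1.2 = 192.

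Both agree with the article.

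**Arm sizes when C clients consent and all are randomised.** Arm 1 = arm 2a = C/2; arm 2b = N − C; so arm 2 = N − C/2.

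- Part B needs C/2 ≥ 192, so C ≥ 384.
- Arm 2 needs N − C/2 ≥ 350, so C ≤ 2(N − 350).
- N = 548: C from 384 to 396, that is 70.1% to 72.3%. Decliners must number 152 to 164.
- N = 542 (892 − 350): C ≤ 384, so both sizes are met only at C = 384 (70.8%), with 158 decliners.

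**Power, N = 548.** Evaluable numbers are enrolled / 1.2. Power = Φ(|p₁ − p₂| / √[p₁(1 − p₁)/n₁ + p₂(1 − p₂)/n₂] − 1.960).

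| Consent | Arm 1 (= 2a) | Arm 2 | Part A power | Part B power |
|---|---|---|---|---|
| 50% | 137.0 | 411.0 | 83.5% | 65.9% |
| 60% | 164.4 | 383.6 | 82.1% | 73.8% |
| 70% | 191.8 | 356.2 | 80.6% | 80.1% |
| 75% | 205.5 | 342.5 | 79.7% | 82.7% |
| 80% | 219.2 | 328.8 | 78.7% | 85.0% |
| 85% | 232.9 | 315.1 | 77.7% | 87.1% |
| 100% | 274.0 | 274.0 | 74.2% | 91.8% |

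Worked line for full consent: n₁ = 274/1.2 = 228.3 and n₂ = 350/1.2 = 291.7. The standard error is √(0.21/228.3 + 0.16/291.7) = 0.0383, and Φ(0.1/0.0383 − 1.960) = 74.2%.

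Part A power stays at 78% or more up to about 84% consent.

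**With randomisation stopped at 384.** Arm 2 = 548 − 192 = 356, Part A power about 80.5%; or 542 − 192 = 350, about 80.2%. This holds at any consent of about 70% or more.

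**Sensitivity.** If 20% of those enrolled are lost (multiply by 0.8 instead of dividing by 1.2), Part A power is 76.1% at 85% consent and 72.5% at 100%.

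**The case against.** Three objections have weight.

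1. **The lower limit is disclosed.** At most 164 decliners out of 548 is the same statement as at least 70.1% consent. A reader might infer that the plan claims 80% power for both parts while hiding a narrow 70–72% window. The documents do not support that. The large losses (66% in Part B at 50% consent, 74% at 60%) all lie on the disclosed side and follow from missing a stated target. Only the upper limit is unstated.

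2. **A cap may be intended.** The total counts arm 1 as exactly 192, which fits recruiting Part B to target and then stopping. The randomisation section describes how consenters are allocated, not when recruitment ends, and the full protocols, not shown here, may set the limit. So it cannot be said that no cap exists. What stands is that the article states none, and that its allocation followed as written does not preserve the 350 at high consent.

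3. **The undisclosed loss is small.** A reader might infer that Part A is seriously underpowered. It is not: power is 1 to 2 points short up to about 84% consent, and 74.2% needs consent from every client, although the design expects some to decline.

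**Conclusion.** The point holds as a limited one. On the article's stated allocation, arm 2 falls below 350 once consent exceeds 72.3% (N = 548) or 70.8% (N = 542), so at least 152 of the 164 (or all 158) are needed to fill arm 2. The cost to Part A is modest, about 79.7% power at 75% consent and 74.2% at worst. This rests on every consenter being randomised, arm 3 staying at 350, the article's own response rates, and its 1.2 inflation.

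Separately, the intake figures disagree: 548 + 350 = 898, not 892.

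**What to change.** - State that Part B randomisation stops at 384, and that PHC clients enrolled later stay in arm 2, with the definition of 2b widened to include them.
- Reconcile 548 with the 542 implied by 892, and correct the margin to match: 164 if 548, 158 if 542 (542 − 384).
- Replace the margin sentence with one that says Part B's 80% power depends on about 70% consent, with about 74% power at 60% and 66% at 50% (figures for N = 548).

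**Cost:** one recruitment rule and a reworded paragraph, with no extra participants. There are two downsides. Part B cannot grow beyond plan if consent is high, and 2b would then mix decliners with late-enrolled clients who were never offered Part B. The cap does nothing for Part B if consent is low; there the remedy is only to state the dependence.
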